## Sample size

Sample size calculations were based on an equivalence study design [35] and the primary outcome measure (completeness of survey responses). Given the current follow up response rates from the PCOR-VIC we estimate that we will achieve a response rate of 90% [32] when PROMs are administered by the telephone follow-up method. The study was designed to evaluate whether the completeness of survey responses in the ‘mail/postal service group’ or ‘email group’ was similar to the ‘telephone’ group. Assuming that the equivalence margin is 10%, we will require 190 respondents per group. We have made an assumption that the 83% of who have internet access will also have an email account [36]. The sample size was adjusted accordingly so the final number of respondents required in each group is 229 giving a total number required n = 687 (Table 1). Our sample size has been calculated to provide a level of significance at 5% with 80% power (2-sided test). The sample size calculation was performed in Stata V13.0 [37].

**Table 1 Tab1:** Sample size calculation

Indicator	Targeted response rate	Equivalence margin	Sample size (SS) per group	Internet access	SS adjusted for email	Total Sample required
Response rate	90%	10%	190	83%	229	687

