**Methods/design:**

This study will adopt an equivalence randomised controlled design. Participants are men diagnosed with and/or treated for prostate cancer (PCa) participating in PCOR-VIC and meet the criteria for 12-month follow-up. Participants will be individually randomized to three independent groups: telephone, mail/postal, or email to complete the 26-item Expanded Prostate Cancer Index Composite (EPIC-26) survey. It is estimated each group will have 229 respondents. We will compare the proportion of completed surveys across the three groups.

The economic evaluation will be undertaken from the perspective of the data collection centre and consider all operating costs (personnel, supplies, training, operation and maintenance). Cost data will be captured using an Activity Based Costs method. To estimate the most cost-effective approach, we will calculate incremental cost-effectiveness ratios. A cost projection model will be developed based on most cost-effective approach for nationwide scale-up of the PROMs tool for follow-up of PCa patients in Australia.

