### Trial design

The study design proposed for this evaluation is an equivalence RCT design. Participants will be individually randomized to one of three independent groups receiving the PROMs instrument by email, post or by telephone. Due to the nature of the intervention, it is not possible to blind the researchers or study participants.

To collect costing data we will use an Activity Based Costing (ABC) method [33] and structured questionnaires to estimate the cost of the operational activities of the three different methods of follow up. The ABC method is useful for understanding key activities of any programs and interventions and allows identification of (i) implementation levels and composition of costs; (ii) variations in how an intervention is implemented over time and associated cost implications; and (iii) resulting costs of increasing coverage of cost-effective data collection methods. This method is flexible, so its resulting estimates can be easily understood and adapted to measure the cost of data collection of the three different methods. Costs that will be considered include personnel cost, cost of supplies (e.g., envelopes, printing etc.), cost of training of data collectors and cost of operation and maintenance (e.g., telephone bill, internet bill, rent etc.) for each of the data collection methods.

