Telephone costs – all receive initial phone call, plus telephone costs for collection via the telephone.	Yes	Yes	YesMethodology of time allocation of providersData collectors will maintain a spreadsheet to record the time spent for each data collection method. The time will be categorised into direct data collection and non-service professional activities which includes preparatory activities, maintaining and management of records and information, and obtaining supplies.
*Calculating Total and Average Costs:*
We will sum personnel costs, cost of supplies, training costs and costs of operation and maintenance to provide a total cost for each of the follow up methods as well as average cost for each constituent items.
*Estimating cost effectiveness*
To estimate the most cost-effective approach, incremental cost effectiveness ratios (ICERs) will be estimated. This involves comparing the incremental/additional cost of one approach with the additional outcome achieved by using that approach. Outcome will be measured as completed surveys. The most cost effective approach will be the method which achieves the greatest percentage of complete surveys at the least cost [42]. Scenario analysis will be undertaken to test some of the assumptions in estimating the cost of each approach.

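### The trial is sized for two-sided equivalence to telephone, although for mail and email against telephone only the lower limit matters; non-inferiority with the same men and margin would have about 90% power instead of 80%

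*Protocol article*

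**What the plan says.** The design is called equivalence throughout. The Abstract states "This study will adopt an equivalence randomised controlled design", the Trial design section "The study design proposed for this evaluation is an equivalence RCT design", and the Sample size section "Sample size calculations were based on an equivalence study design"; the end of the Background uses the same term.

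The Sample size section asks whether completeness by mail or by email is similar to completeness by telephone. It plans 90% completion by telephone, a 5% two-sided level and 80% power, and continues: "Assuming that the equivalence margin is 10%, we will require 190 respondents per group". Dividing by an assumed 83% with internet access gives 229 per group and 687 in total (Table 1).

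Three other places bear on the choice of hypothesis:

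- The Background says that the survey is at present administered only by telephone, with a current response rate of 85%.
- The Economic analysis section defines the preferred mode: "The most cost effective approach will be the method which achieves the greatest percentage of complete surveys at the least cost". The Discussion leaves the choice to the steering committee and the funder, who weigh cost against completeness.
- The Data analysis plan compares each pair of arms by a z test of the difference at P < 0.05. It refers to no margin.

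**The concern.** An equivalence hypothesis treats a departure in either direction as a failure. Here the directions are not alike. Mail and email are alternatives to the mode in use, and the protocol's criterion for choosing a mode credits higher completion; no section counts it against a mode. For mail or email against telephone, the question that serves the choice is whether the new mode loses 10 points or more.

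The sample size nevertheless gives half of its type II error to the upper limit. At the planned 90% that limit lies at 90% + 10 points = 100%. What is at stake is power for the useful question, and how the result would read if the stated equivalence margins were applied: a mode that completes more surveys than telephone could be reported as not equivalent.

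**Working it through.** **Inputs.** Completion 90% by telephone (Sample size; Table 1). The same 90% for mail and email is not stated separately; it is inferred from the single target rate in Table 1 and it reproduces the plan's figure. Margin 10 points, two-sided 5% (1.960 at each limit), power 80%, email factor 83%.

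**1. The plan's own figure.** Equivalence, with the 20% type II error split as 10% per limit (z = 1.282):

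n = 2 × 0.9 × 0.1 × (1.960 + 1.282)² / 0.10² = 189.1, rounded up to 190.

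190 / 0.83 = 228.9, so 229; 229 × 3 = 687. All three figures reproduce. Other readings do not give 190: two one-sided tests at 5% each give 155, and a superiority test of 90% against 80% gives 199. Both limits were therefore sized for.

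**2. The one-sided question.** Non-inferiority at one-sided 2.5% and 80% power:

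n = 0.18 × (1.960 + 0.842)² / 0.01 = 141.3, so 142 per group.

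**3. Power with the planned numbers.** Normal approximation at 190 per group: standard error = √(0.18/190) = 0.0308, and 0.10/0.0308 − 1.960 = 1.289. Power at the lower limit is Φ(1.289) = 90%. Each limit fails in 9.9% of trials, so equivalence has 80%.

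Exact binomial enumeration with unpooled Wald 95% intervals agrees. Completion is given as new mode / telephone:

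| True completion | n per group | Non-inferiority shown | Equivalence shown | Fails on upper limit only |
|---|---|---|---|---|
| 90 / 90 | 190 | 90.0% | 80.0% | 10.0% |
| 90 / 90 | 229 | 94.5% | 88.9% | 5.5% |
| 85 / 85 | 190 | 77.9% | 55.8% | 22.1% |
| 85 / 85 | 229 | 85.2% | 70.5% | 14.8% |
| 87 / 90 | 190 | 57.5% | 55.3% | 2.2% |
| 87 / 90 | 229 | 65.5% | 64.7% | 0.8% |
| 93 / 90 | 190 | 99.5% | 68.4% | 31.1% |

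In the 90 / 90 rows, every trial that fails on the upper limit has the new mode observed above telephone. The cost of the upper limit is 10 points of power at 190 and 5.5 points at 229 when the modes are equal at 90%. It is about 2 points or less when the new mode is 3 points lower, and it grows when the new mode is better.

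**The case against.** **No harm follows from the protocol as written.** A reader might infer that a mode better than telephone would often be turned down. The documents do not support that. No section makes acceptance depend on passing an equivalence test: the primary analysis tests a difference without a margin, and the choice rests on cost and completeness. A mode with higher completion would be favoured. This stands, so the harm is potential: it arises if the stated margins are applied to the results.

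**The upper limit is not always out of reach.** A reader might infer from 90% + 10 points = 100% that it guards against something that cannot happen. That holds only at the planned 90%. At the 85% in the Background the limit is 95%, which can be exceeded.

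**Large gains for the new modes have little support.** The cited background points to lower completion by email and by post, although the telephone follow-up of non-responders in both arms may narrow the gap. If the new mode is somewhat lower, the upper limit hardly matters. This stands and limits the benefit to modes that are equal or better.

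**The upper side may have some use.** The size of a gain enters the cost-effectiveness ratio, and the documents do not establish that mail and email will be cheaper: one cited study found internet surveys almost twice as costly as personalised post. Mail versus email has no reference arm, so a symmetric comparison is natural there. Both points stand. They argue for reporting an estimate with its interval, and for confining non-inferiority to the two comparisons with telephone.

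**Nothing is miscalculated.** True. The design is named consistently, the numbers reproduce, and for the lower limit the trial is larger than it needs to be.

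**Conclusion.** The concern holds as a cheap improvement to the design, not as an error of calculation. For mail and email against telephone the lower limit is the one that matters. With both arms at 90%, the planned numbers give about 90% power for non-inferiority against 80% for equivalence at 190 per group, and about 95% against 89% at 229. With both arms at 85%, the figures are about 78% against 56%, and 85% against 70%. If the new mode is truly a few points lower, almost nothing is gained.

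This rests on three assumptions: equal true completion for the main figures, Wald 95% intervals, and the reading that higher completion is welcome. The last is inferred from the criterion for choosing a mode and from telephone being the incumbent; the protocol sets no margin-based rule. It would weaken if a new mode proved dearer than telephone.

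**What to change.** - In the Abstract, the Background, the Trial design and Sample size sections and Table 1, state the hypothesis as non-inferiority of mail and of email to telephone. Keep the 10-point margin, the one-sided 2.5% level and 190/229 per group.
- In the Data analysis plan, replace the z test of the difference for these two comparisons by the two-sided 95% confidence interval for mode minus telephone. The mode is non-inferior if the lower limit is above −10 points, and superior if it is above 0.
- Report mail versus email as a difference with its 95% confidence interval.
- Restate the power as about 90% at 190 and 95% at 229 per group if both arms are at 90%, and about 78% and 85% if both are at 85%.

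The cost is wording in the protocol, and in the registry entry if it repeats the design label; no further men or data are needed. The trial gives up the claim that a new mode is not better than telephone by 10 points or more. That would matter only if the mode proved dearer, and the estimate with its interval would still enter the cost-effectiveness ratio.

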## Randomisation process

Figure 1 illustrates the different steps for following up patients on the PCOR-VIC registry to complete the PROM (EPIC-26 survey). The first step after data collectors’ telephone to men is to confirm treatment and GP details and obtain the most recent PSA result. If the patient is contacted within the window from 21 days before the “Anniversary Date”, then they will be eligible for randomization. Randomization will be undertaken using random permuted blocks of sizes 3 and 6 [38]. The investigator will have already generated the random blocks and provide those to the data collectors in sealed envelopes. Once the data collector has confirmed the patient’s PSA result, GP details and eligibility for 12-month follow-up then s/he will proceed with selecting a random number from the sealed envelope to assign the method for collection of data by EPIC-26 survey. If a patient has been assigned to the email method but, when the data collector asks for an email address and the patient replies that he does not have one, the data collector will select the next and subsequent envelopes until either the telephone method (Intervention A) or mail/postal methods (Intervention B) is assigned.

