## Data analysis plan

### Primary and secondary outcomes

For the primary outcome measure (completeness of surveys), we will estimate individual proportions with 95% CI for each arm of the trial. We will then calculate the pooled sample proportions for each pair and the standard error of the difference. Using these measures, we will calculate the Z score test statistics. The p value will be reported for the difference and P < 0.05 will be considered as statistically significant.

For the secondary outcome measures, we will carry out independent sample t-tests to detect the difference.

Analysis will be conducted by intention to treat (ITT) [39] as well as per protocol method [40]. The ITT method will allow us to evaluate the effect of each intervention in a real life situation (i.e. when subjects are randomized to the ‘email group’ but end up in the ‘telephone’ or ‘mail’ methods instead). The per-protocol method will allow us to study the direct effect of each option.

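### Email access is asked only after an email envelope is drawn, so the per-protocol comparison does not show the direct effect of email, and ITT dilutes it

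*Protocol article*

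**What the plan says.** Under Randomisation process, the collector confirms the PSA result, GP details and eligibility, then opens an envelope. "Randomization will be undertaken using random permuted blocks of sizes 3 and 6", which implies 1:1:1 allocation. Email access is not among the checks listed before the draw. It comes up only afterwards: "If a patient has been assigned to the email method but, when the data collector asks for an email address" and the man has none, "the data collector will select the next and subsequent envelopes until either the telephone method (Intervention A) or mail/postal methods (Intervention B) is assigned". The description of Intervention C likewise sends men without email at random to telephone or mail. Nothing in the text records email access for men who draw telephone or mail directly.

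Under Sample size: "Assuming that the equivalence margin is 10%, we will require 190 respondents per group". Then: "We have made an assumption that the 83% of who have internet access will also have an email account". And: "The sample size was adjusted accordingly so the final number of respondents required in each group is 229", or 687 in total.

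The data analysis plan announces both ITT and per-protocol analyses. ITT is meant to reflect real life, including men randomised to email who end up on another method. Of the other analysis it says: "The per-protocol method will allow us to study the direct effect of each option".

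**The concern.** Having an email address is in effect an eligibility condition for one arm, yet it is applied after allocation and only to men who draw that arm. Removing men from one arm on a patient characteristic, and moving them into the other two, undoes randomisation for any comparison by method received. If men with and without email differ in how readily they complete a survey, the per-protocol contrast mixes that difference with the effect of the mode.

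ITT does not have this imbalance, but part of its email arm is surveyed by a comparator method. That pulls the arms together, and in an equivalence trial this favours the claim under test. Both comparisons with email on the primary outcome, and the choice of method for national scale-up, rest on these analyses.

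**Working it through.** **Inputs from the protocol.** Telephone rate 90%; margin 10 points; 5% two-sided; 80% power; 83% with email, so 17% without; blocks of 3 and 6; 687 men.

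**Assumptions not in the protocol.** The two block sizes are equally likely. Opened envelopes are used up. The completion gap between men with and without email is 5 to 20 points.

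**1. The plan's sample size.** n = 2p(1−p)(z₀.₉₇₅ + z₀.₉₀)²/margin² = 2 × 0.9 × 0.1 × (1.960 + 1.282)²/0.1² = 189.1, so 190. Then 190/0.83 = 228.9, so 229, and 3 × 229 = 687. All three figures reproduce. The inflation shows that about 17% of the email arm was expected not to receive email.

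**2. Who ends up where.** A hand approximation with independent draws:
- Email delivered: 687 × 0.83/3 = 190.
- Telephone, and likewise mail: (687 − 190)/2 = 248.5.
- Men without email in each of these: 687 × 0.17/2 = 58.4, or 58.4/248.5 = 23.5%.

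Simulating the written rule with blocks (2,000 runs) gives these means:

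| | Telephone | Mail | Email |
|---|---|---|---|
| First draw | 225 | 225 | 237 |
| Method delivered | 245 | 245 | 197 |
| No email, by first draw | 17% | 17% | 17% |
| No email, by method delivered | 24% | 24% | 0% |

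If per-protocol drops the redrawn men, the contrast is 17% against 0%.

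**3. Per-protocol bias with no true mode effect.** Bias = share without email in the comparator × completion gap.

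| Assumed gap | Redrawn men dropped (0.17) | By method delivered (0.239) |
|---|---|---|
| 5 points | 0.9 | 1.2 |
| 10 points | 1.7 | 2.4 |
| 20 points | 3.4 | 4.8 |

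Email is flattered if men without email complete less often, and penalised if they complete more often.

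**4. ITT by first draw.** Email access is balanced. If redrawn men complete at the telephone rate, a mode difference D appears as 0.83 × D. A true 10-point deficit shows as 8.3, and one of 10/0.83 = 12.0 shows as 10.0. Take equivalence as a 95% CI inside ±10 points (normal approximation). At a true 10-point deficit (80% against 90%) the chance of declaring it is 2.5%. Diluted to 81.7% against 90% with 229 per group, it is 7.6%.

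**5. Can the effect be recovered afterwards?** First-draw arms are exchangeable, and the men without email in the email arm are known. So telephone completion in men with email = (telephone rate − share × telephone rate of redrawn men)/(1 − share). In simulation with a true deficit of 10 points and a 20-point gap, this returns about −9.9 points with SD about 4.1, against SD 3.2 for the ITT difference. It rests on about 237 × 0.17/2 = 20 redrawn men surveyed by telephone.

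**The case against.** The strongest defence is that ITT by first draw answers the question the protocol sets for it: what happens when men are assigned to email and those without it fall back on another method. For a population-based registry that is a sensible question, and for it ITT is unbiased. This stands, provided that the first draw is recorded and used. A reader might infer that both analyses are biased outright. The documents do not support that: ITT is diluted for email as a mode, not confounded.

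A reader might also infer that the per-protocol bias can never be repaired. It can, from the redirected men, with the loss of precision shown above.

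Other stronger readings fail too:
- The plan did not expect 229 men surveyed by email. It expected 229 × 0.83 = 190, and the written rule delivers about 197.
- Nothing says that opened envelopes return to the pile, so redraws do not show collectors the allocation of later men.
- Language skills are a poor explanation for a completion gap, since men who do not speak English are excluded.

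Finally, the article is condensed and its flow chart is not shown, so email access might be recorded elsewhere. Even so, the order described is explicit: the question follows the draw. None of this rescues the per-protocol sentence, because that is the analysis offered for the mode effect and it is the one subject to selection.

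**Conclusion.** The point holds for email as a mode, meaning the Intervention C sequence including its later telephone calls. The imbalance of 0% against 17% to 24% without email follows from the written rule and the 83%. The per-protocol sentence is therefore wrong as it stands. The bias of about 0.9 to 4.8 points rests on the assumed 5-to-20-point gap, and its direction is unknown. The ITT dilution to 0.83, and the rise from 2.5% to about 7.6%, rest on redrawn men completing at the telephone rate. The sample size is not in error, and ITT by first draw remains valid for the policy of email with fallback.

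**What to change.** - Ask every man for an email address, and record the answer, before any envelope is opened.
- Use two envelope sets without redraws: 1:1:1 for men with email, and 1:1 to telephone or mail for men without.
- Estimate the effect of email as a mode within men with email. From 687 men this gives 687 × 0.83/3 = 190 per arm, the number the plan requires (80.3% power at equality).
- Compare mail with telephone in all men, stratified by email access: about 190 + 58 = 248 per arm.
- Keep the real-life policy comparison by combining the two strata, weighted by their observed shares. Men without email contribute to both sides of that contrast, so its variance must allow for this.
- Reword the per-protocol sentence so that it no longer promises the direct effect of each option.

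The cost is one more question per call, a second envelope set and a few sentences of analysis text, with no more men if 83% have email. The mode conclusion then applies to men with an email address; the weighted policy comparison covers the rest.

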**Fig. 1 Fig1:**
[figure not shown]
Flow chart showing 3 different follow-up methods

### Description of intervention(s)/exposure

An attempt will be made to contact all men who have not opted off the registry and meet the eligibility criteria. The details and procedure followed by data collectors for administering the EPIC-26 survey following randomisation to one of the three approaches is described below and presented in Fig. 1 Flow Chart showing 3 different follow up methods.

